##### Objective 2: Characterize the Long COVID Cohort and Compare Profiles With Matched Recovered Controls

Baseline (T0) characteristics will be reported for cases and matched controls using paired summaries (within-pair differences where informative) and standard descriptive statistics (means [SD] or medians [IQR] for continuous variables and frequencies and percentages for categorical variables). Distributional assumptions will be checked (eg, Shapiro-Wilk for guidance, complemented by graphical inspection).

##### Objective 3: Evaluate Symptom and Outcome Evolution From T0 to T1

Longitudinal changes in continuous secondary outcomes (eg, questionnaire scores, cognitive test metrics, and selected continuous biomarkers) will be modeled using mixed-effects models including fixed effects for group (case vs control), time (T0 vs T1), and the group × time interaction to estimate differential change over time, with random intercepts for participants and appropriate correlation structures. Binary/ordinal outcomes will use generalized mixed-effects models with appropriate links (logit for binary; ordinal models for ordered scales where applicable). Primary longitudinal contrasts will be (1) within-group change and (2) between-group difference in change (interaction term), each reported with 95% CIs.

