### Matching Strategy

Recovered controls will be individually matched 1:1 to Long COVID cases without replacement to improve baseline comparability. Matching will require exact matching on sex/gender, with flexibility of ±3 years for age and ±30 days for date of acute COVID-19 diagnosis. When multiple eligible controls are available for a given case, the selected control will be the one minimizing the absolute age difference; if ties remain, the absolute diagnosis date difference will be minimized, with random selection used only if ties persist. Each matched set will be assigned a unique pair identifier (pair_id) and retained in the analytical dataset; participants who cannot be matched within the prespecified calipers will be retained in the study database and considered in prespecified sensitivity analyses.

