**Sociodemographic**
Age, sex/gender, place of residence, occupation, education level, and ethnicity

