#### Secondary Outcomes

Secondary outcomes will encompass patient-reported and performance-based domains including health-related quality of life, physical activity, dietary pattern/adherence, sleep quality, depressive and anxiety symptoms, post–COVID-19 functional status, cognitive performance, as well as pain catastrophizing, fatigue severity, and laboratory biomarkers (biochemistry/hematology/coagulation, inflammatory markers including C-reactive protein [CRP] and IL-6, cytokine profiling, SARS-CoV-2 serology, and viral reactivation serologies such as Epstein-Barr virus [EBV], cytomegalovirus, and herpes simplex virus type 1 [HSV-1]). The presence and severity of persistent symptoms consistent with Long COVID (eg, fatigue, dyspnea, and cognitive complaints), will be operationalized using standardized symptom assessment procedures within the Long COVID group and contrasted with the absence of persistent symptoms in the control group. Symptom severity will be quantified using the prespecified instruments and scales described in the “Sociodemographic and Clinical Variables” section, enabling both between-group comparisons at each time point and within-participant change from T0 to T1.

These outcomes will be analyzed as complementary indicators of disease burden and functioning and as potential correlates of persistent symptom status and its evolution over time.

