### Planned Reporting of Findings

Primary analyses will compare matched Long COVID and recovered participants using methods that account for the paired design (eg, conditional logistic regression with pair strata) and will evaluate longitudinal change using mixed-effects models including group, time, and group × time interaction. The first manuscripts reporting baseline comparisons and longitudinal outcomes are planned for submission in the second half of 2026, followed by mechanistic/biomarker and predictive modeling outputs.

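### The mixed models for secondary outcomes carry no antecedent covariates, so case-control differences in level at T0 or T1 would absorb recorded but unmatched differences in education and preinfection comorbidity

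*Protocol article*

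**What the plan says.** Objective 3 of the Statistical Analysis section models continuous secondary outcomes with "mixed-effects models including fixed effects for group (case vs control), time (T0 vs T1), and the group × time interaction", "with random intercepts for participants and appropriate correlation structures". Binary and ordinal outcomes get the generalized counterpart. Planned Reporting of Findings says that the study "will evaluate longitudinal change using mixed-effects models including group, time, and group × time interaction". Neither place names a covariate.

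The contrasts that Objective 3 puts first are changes: "Primary longitudinal contrasts will be (1) within-group change and (2) between-group difference in change (interaction term), each reported with 95% CIs". The Secondary Outcomes section goes further and describes symptom severity measurement as "enabling both between-group comparisons at each time point and within-participant change from T0 to T1". Level differences at T0 and at T1 are therefore also intended.

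On comparability of the groups, Matching Strategy states: "Matching will require exact matching on sex/gender, with flexibility of ±3 years for age and ±30 days for date of acute COVID-19 diagnosis". Textbox 1 records "Age, sex/gender, place of residence, occupation, education level, and ethnicity" together with comorbidities, and the Sociodemographic and Clinical Variables section gives confounding control as one reason for recording comorbidities. An a priori core adjustment set does appear, but under Objective 1, for the conditional logistic model of Long COVID status. Its examples are acute severity, vaccination and comorbidity burden; education is not among them. Objective 2 is descriptive: "Baseline (T0) characteristics will be reported for cases and matched controls using paired summaries (within-pair differences where informative) and standard descriptive statistics".

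**The concern.** In Objective 1 the group label is the outcome and antecedent factors are explanatory. In Objective 3 the roles reverse: group explains a test score, questionnaire score or biomarker. Any antecedent factor that differs between groups and also predicts that score is then a confounder of the level difference. The study expects such differences. Its own hypothesis is that sociodemographic factors and preinfection comorbidities are associated with Long COVID status. Some cases come from a voluntary patient association, and the Limitations section concedes selection bias.

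At stake is the reading of a between-group difference at T0 or T1. A cognitive deficit in cases could be exaggerated if cases have less education than controls, or hidden if they have more. The direction cannot be known from the article. A larger sample does not remove the problem: the bias stays fixed while the standard error shrinks.

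**Working it through.** **The plan's own figure.** The only design figure is the sample size. A control prevalence of 20% with an odds ratio of 2.3 gives case odds 2.3 × 0.25 = 0.575 and prevalence 0.575/1.575 = 0.365. The pooled-variance formula with two-sided alpha 0.05 and 90% power gives 154.2, hence 155 per group, which agrees with the article. The present point does not depend on it.

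**Inputs.** From the article: the fixed effects, the matching variables and 100 participants per group enrolled. Assumed, because the article gives neither: a binary antecedent factor (say, higher education) with effect b on an outcome of SD 1, and a prevalence difference d between groups.

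**Level difference.** With complete data at two time points, the group estimate at a given time is the difference in raw means. Without a true group effect its expectation is b × d.

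| b (SD) | d = 0.10 | d = 0.20 | d = 0.30 |
|---|---|---|---|
| 0.3 | 0.03 | 0.06 | 0.09 |
| 0.5 | 0.05 | 0.10 | 0.15 |
| 0.8 | 0.08 | 0.16 | 0.24 |

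For scale, take a single-time, unpaired comparison with 100 per group. The SE is √(2/100) = 0.141, and a 5% test of no difference rejects with probability Φ(−1.96 + bias/SE) + Φ(−1.96 − bias/SE).

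- Bias 0.03: ratio 0.21, rejection 5.5%.
- Bias 0.10: ratio 0.71, rejection about 11%.
- Bias 0.24: ratio 1.70, rejection about 40%.

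At 200 per group (the target of about 400) the SE is √(2/200) = 0.10, and the same biases give about 6%, 17% and 67%.

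**Difference in change.** The factor contributes b₁ × d at T1 and b₀ × d at T0, so the group × time term carries (b₁ − b₀) × d. If the effect is constant this is exactly 0. If it grows from 0.5 to 0.7 SD with d = 0.20, it is 0.2 × 0.2 = 0.04 SD. A main effect of the factor cannot remove that; a factor × time term can.

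**Simulation.** A random-intercept model was simulated with no true group effect, b = 0.5, and 50% of controls against 30% of cases having the factor (150 data sets per setting).

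| Per group | Group level difference, unadjusted | Adjusted for the factor | Group × time, with or without the main effect |
|---|---|---|---|
| 100 | −0.11 | −0.01 | +0.02 |
| 155 | −0.095 | +0.01 | −0.01 |

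Monte Carlo error is about 0.01 (for the level at 100 per group, 0.141/√150 = 0.012). The level bias agrees with the algebra (0.10 SD) and disappears on adjustment. The group × time estimate is the same whether or not the main effect is included. With the effect rising to 0.7 SD at T1 and 100 per group, the group × time estimate was −0.05, and −0.01 once the factor × time term was added.

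**The case against.** The strongest reply is that the quoted model serves change, not level. Its declared primary contrasts are within-group change and difference in change, and a fixed factor with a constant effect drops out of both. That stands. A reader might infer from the missing covariates that every case-control contrast in these models is confounded; the article does not support this. The difference in change is at risk only if education or comorbidity also affects change over the roughly 3 years, or drives dropout. Nor does a time-constant main effect buy meaningful precision for within-person change.

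Second, a reader might infer that T0 differences are never adjusted. Under Objective 1 the lifestyle/psychosocial and biomarker blocks enter a conditional logistic model with a core set that includes comorbidity burden, so an adjusted case-control association is planned for those measures. This also stands. It does not, however, yield an adjusted difference in any outcome, it does not address T1, and education is not named there.

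Third, the article says that the models include these terms, which leaves room for others, and a condensed article may leave covariates to a fuller plan. That the models contain nothing else is therefore an inference. But the same list appears twice, and the article is specific about adjustment for Objective 1, so an analyst following the text would fit the unadjusted model.

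Finally, the article disclaims causal interpretation and calls T0 measures phenotypic correlates. Unadjusted description is compatible with that aim, which is why Objective 2 needs no change. Even as an association, though, a level difference is hard to read as a feature of Long COVID if it may partly reflect schooling or earlier illness.

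**Conclusion.** The point holds for between-group differences in level at T0 or T1 read from the Objective 3 models, most plainly for cognitive scores. As specified, those differences would absorb case-control differences in recorded but unmatched antecedent factors. Under the assumed range the bias is 0.03 to 0.24 SD, in either direction. The low end is negligible; the high end could by itself produce a nominally significant result. The range is an illustration, because the article reports no imbalance and no effect of education or comorbidity on any outcome; that education influences the cognitive tests is itself an assumption.

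The point does not extend to within-group change, nor to the group × time term while the factor's effect is constant and dropout is unrelated to it. It is a worthwhile and cheap improvement, not a flaw in the declared primary longitudinal contrasts.

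**What to change.** In Objective 3, and to match in Planned Reporting of Findings:

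- For between-group contrasts in level at T0 or T1, add a prespecified antecedent set, education and preinfection comorbidity, as fixed effects.
- For the difference in change, add education × time and comorbidity × time as an adjusted analysis.
- Keep postinfection variables out of this set. The Objective 1 core set should not be copied over whole, because it includes acute severity. Incident comorbidities, which the study also records, should be left out too.
- Report the unadjusted estimates beside the adjusted ones.

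Leave the descriptive summaries under Objective 2 as they are.

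The variables are already part of data collection and the primary analyses follow completion of T1, so this is a change of wording. The cost is a few degrees of freedom and a second set of estimates to present.

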#### Analysis of Populations and Data Structure

The primary analytical dataset will consist of 1:1 matched pairs of Long COVID cases and recovered controls, with matching performed without replacement on sex/gender (exact), age (±3 years), and date of acute COVID-19 diagnosis (±30 days), and a retained pair_id. Data will be organized (1) in wide format for descriptive summaries by group and time point and (2) in long format (1 row per participant per time point) for longitudinal models incorporating T0 and T1.

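### The longitudinal mixed models name no pair effect, so case-control differences at a single time point, mainly T1, would get somewhat too wide confidence intervals

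*Protocol article*

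**What the plan says.** All references are to the protocol article.

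- **Objective 3** gives the longitudinal model "fixed effects for group (case vs control), time (T0 vs T1), and the group × time interaction to estimate differential change over time". Its random part is described only by the words "with random intercepts for participants and appropriate correlation structures". Binary and ordinal outcomes get generalized mixed models. It then states: "Primary longitudinal contrasts will be (1) within-group change and (2) between-group difference in change (interaction term), each reported with 95% CIs". Neither the pair nor any matching variable (sex/gender, age, diagnosis date) is listed.
- **Planned Reporting of Findings** repeats the model in short form: the study "will evaluate longitudinal change using mixed-effects models including group, time, and group × time interaction".
- **Matching Strategy**: "Each matched set will be assigned a unique pair identifier (pair_id) and retained in the analytical dataset". **Analysis of Populations and Data Structure**: "The primary analytical dataset will consist of 1:1 matched pairs of Long COVID cases and recovered controls", with matching on the three variables "and a retained pair_id". The same section sets up the long-format data for the longitudinal models.
- **Secondary Outcomes** describes the symptom severity measures as "enabling both between-group comparisons at each time point and within-participant change from T0 to T1".
- **Pairs are used elsewhere.** Objective 1 plans McNemar, paired t or signed-rank tests and conditional logistic regression with the pair as stratum. Objective 2 plans paired T0 summaries. The prediction section keeps pair members in the same fold.
- **Missing Data, Multiplicity, and Sensitivity Analyses** mentions adjustment for the matching variables only where unmatched participants are brought in.

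**The concern.** Matching on age, sex/gender and diagnosis date tends to make the two members of a pair alike on any outcome that depends on those variables; cognitive scores and some laboratory values are likely examples. A model whose only random effect is the participant absorbs that shared variation into the between-participant variance. It then computes the case-control difference at a given time point as if the two groups were independent samples, so the standard error comes out too large.

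At stake is the precision of those single-time-point differences. At T0 the paired tests of Objective 1 and the paired summaries of Objective 2 already use the pairs. At T1 no paired analysis is named, so the Objective 3 model is the only named route to a case-control difference there. Precision is worth keeping: Recruitment and Follow-up Progress reports 100 per group enrolled, against a minimum of 155 per group.

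**Working it through.** **The plan's own figure.** The article gives no standard error, correlation or power for the longitudinal model. Its only power figure is for two independent proportions. With 20% in controls and an odds ratio of 2.3, the case prevalence is 0.2 × 2.3 / (0.8 + 0.2 × 2.3) = 0.46 / 1.26 = 0.365. Two-sided α = 0.05 and 90% power then need 155 per group (power 0.8996 at 154, 0.901 at 155). The stated figure reproduces, but it does not bear on the model at issue.

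**Inputs.** n = 100 pairs (current enrolment). Outcome variance is set to 1, so results are in SD units. Assumptions, since the article gives neither value: within-pair correlation ρ from 0.05 to 0.30, and within-person correlation r = 0.6 between T0 and T1.

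**Case-control difference at one time point.**
- Without a pair term: SE = √(2/n) = √(2/100) = 0.141.
- With a pair intercept: SE = √(2(1−ρ)/n).
- Ratio: 1/√(1−ρ).
- Coverage of the nominal 95% interval without the pair term: 2Φ(1.96/√(1−ρ)) − 1.
- Power is for a true difference of 0.4 SD, an illustrative value that is not in the article.

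| ρ (assumed) | SE with pair term | SE without | Excess | Coverage without | Power without / with |
|---|---|---|---|---|---|
| 0.05 | 0.138 | 0.141 | 2.6% | 95.6% | 81% / 83% |
| 0.10 | 0.134 | 0.141 | 5.4% | 96.1% | 82% / 85% |
| 0.20 | 0.126 | 0.141 | 11.8% | 97.2% | 83% / 89% |
| 0.30 | 0.118 | 0.141 | 19.5% | 98.1% | 85% / 92% |

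Coverage above 95% means a rejection rate below 5% under the null.

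**Declared primary contrasts.** A constant pair effect is the same at T0 and T1, so it cancels in the change.
- Group × time: SE = √(4(1−r)/n) = √(4 × 0.4/100) = 0.1265 with or without the pair term.
- Within-group change: SE = √(2(1−r)/n) = √(0.8/100) = 0.089, likewise.

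**Check by simulation** (100 complete pairs, r = 0.6, 60 runs per ρ, continuous outcome). Mean model standard errors, without versus with a pair intercept:

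| Contrast | ρ = 0.10 | ρ = 0.30 |
|---|---|---|
| T0 group difference | 0.1398 vs 0.1320 | 0.1418 vs 0.1171 |
| Group × time | 0.1257 vs 0.1257 | 0.1276 vs 0.1276 |
| Change in controls | 0.0889 vs 0.0889 | 0.0902 vs 0.0902 |

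These agree with the formulas. Sixty runs are too few to check coverage empirically. Some fits gave convergence or boundary warnings, which bears on the fix. Binary and ordinal models were not simulated.

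**The case against.** **The model is not declared to deliver the affected quantity.** Objective 3 names within-group change and the interaction as its contrasts, and a pair intercept changes neither with complete data. Secondary Outcomes speaks of between-group comparisons at each time point but does not assign them to this model. This stands and sets the low priority. It does not remove the point, because those comparisons are foreseen and no other analysis is named for T1.

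**The open phrase on correlation structures could cover pairs.** It could, and the text does not exclude them. But it follows participant intercepts in a repeated-measures model, so its natural reading is correlation within a person. Planned Reporting attaches the paired-design wording to the case-control comparison and describes the mixed models separately. One clarifying clause would be needed either way.

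**The size is assumed and may be small.** This stands. Matching is on three variables only, and controls are defined by absence of symptoms, so symptom scales may sit near their floor in controls and leave little within-pair correlation.

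**The remedy may not converge.** With two people per pair and two time points, a nested pair variance can be hard to estimate, more so for binary and ordinal outcomes. This stands, and a fallback is needed.

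**Stronger readings a reader might infer.** One is that the precision bought by matching is lost across the study. The article does not support that: the primary objective and the T0 comparisons use the pairs. Another is that the longitudinal results as a whole are unreliable. That is not supported either, since the declared contrasts are essentially unaffected and the error elsewhere is conservative.

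**Conclusion.** The point holds in limited form. As written, the longitudinal models include neither the pair nor the matching variables, although the identifier is kept and the other case-control analyses use it. Fitted that way, single-time-point case-control differences get intervals that are too wide, in practice mainly at T1.

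The size rests on an assumed positive within-pair correlation: about 3% to 12% for 0.05 to 0.20, and about 20% at 0.30. The result covers continuous outcomes and complete pairs. It does not extend to a situation where changes themselves are correlated within pairs. The interaction would then also get too large a standard error (5.4% at a correlation of 0.10, 11.8% at 0.20), and a constant pair intercept would not correct that.

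This is a low-priority improvement, not a threat to validity.

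**What to change.** In Objective 3 and in Planned Reporting of Findings:

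1. Add a random intercept for pair_id, with participants nested in pairs, to the linear and generalized mixed models. This keeps the remaining member of a pair broken by attrition before T1, which a paired test at T1 would drop.
2. State the fallback: where that model does not converge, which is more likely for binary and ordinal outcomes, use age, sex/gender and diagnosis date as fixed effects instead.
3. State that the between-group differences at T0 and T1 are taken from this model.

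The cost is one model term and a few sentences. No new data are needed. The article places the primary analyses after T1 is complete, so the change can still be specified beforehand.

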### Eligibility Criteria

Participants will be included if they have confirmed SARS-CoV-2 infection by polymerase chain reaction, antigen testing, or serology, and are aged ≥18 years. For the Long COVID group, eligibility will require persistence of symptoms for ≥12 weeks after infection onset, consistent with the World Health Organization (WHO) definition. For the control group, complete recovery will be defined as the absence of persistent or new symptoms after COVID-19. Individuals will be excluded if they refuse to participate, report preexisting symptoms similar to Long COVID prior to SARS-CoV-2 infection, or present severe psychiatric disorders or cognitive impairment that preclude informed participation.

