#### Primary Outcome

The primary outcome will be Long COVID status (case vs recovered control). Cases will be defined as individuals with confirmed SARS-CoV-2 infection who report persistent symptoms for ≥12 weeks after infection onset, consistent with the WHO definition. Controls will be defined as individuals with a confirmed SARS-CoV-2 infection who report complete recovery, operationalized as the absence of persistent or new symptoms after COVID-19.

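### For symptom presence the group × time contrast has no finite estimate, because controls are symptom-free at T0 by definition; for symptom-linked scores it is estimable but open to regression to the mean

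*Protocol article*

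**What the plan says.** Under Primary Outcome, recovery in controls is "operationalized as the absence of persistent or new symptoms after COVID-19", and Eligibility Criteria defines it in the same way. Cases are people "who report persistent symptoms for ≥12 weeks after infection onset, consistent with the WHO definition".

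Under Secondary Outcomes, the presence and severity of persistent symptoms are to be "operationalized using standardized symptom assessment procedures within the Long COVID group and contrasted with the absence of persistent symptoms in the control group". The following sentence turns to severity scales, "enabling both between-group comparisons at each time point and within-participant change from T0 to T1". The third secondary objective asks for change in symptoms, as well as in patient-reported outcomes, within each group, and for the trajectories to be compared.

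Objective 3 in Statistical Analysis specifies mixed models with group, time and their interaction, using a logit link for binary outcomes. It then states: "Primary longitudinal contrasts will be (1) within-group change and (2) between-group difference in change (interaction term), each reported with 95% CIs". It makes no exception for outcomes that define the groups.

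For the questionnaires, Variables and Measurements and the overview of Lifestyle and Psychosocial Variables foresee the same instruments at T0 and T1, with no restriction to cases. Limitations covers selection, recall and misclassification, and attrition. It does not mention regression to the mean.

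**The concern.** An outcome that defines the groups at entry cannot then be compared over time between those groups as if its starting value were free to vary. For symptom presence, the control starting value is fixed at zero. A logit model with group × time then has no finite solution, and software would return an arbitrary large number or fail to converge. If controls are also not asked about symptoms at follow-up, new symptoms over about three years are entered as absent without having been looked for.

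For continuous scores that track the symptoms used to classify people, such as fatigue and functional status, the groups may move towards each other without any differential recovery. A reader could take that movement as evidence that cases improved relative to controls.

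**Working it through.** **The plan's own figure.** The article gives no design figure for the longitudinal contrast. Its one computed figure, about 154 rounded to 155 per group, concerns the case-control comparison. It reproduces: odds ratio 2.3 with 20% in controls gives case odds 2.3 × 0.25 = 0.575, a prevalence of 0.575/1.575 = 36.5%, and 155 per group at two-sided 0.05 and 90% power. It is not at issue.

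**Step 1: symptom presence.** On the logit scale,

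interaction = [logit(case T1) − logit(case T0)] − [logit(control T1) − logit(control T0)].

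Control T0 is 0% by definition, so logit(control T0) is minus infinity. With any symptoms in controls at T1, the interaction has no finite value. A random intercept does not supply the missing information.

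As an illustration, take 100 per group (the current enrolment), T0 at 100% in cases and 0% in controls, and assume T1 prevalences of 60% and 10%. Adding a small constant to each cell gives:

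| Constant added | Interaction (log odds ratio) |
|---|---|
| 0.5 | −8.1 |
| 0.1 | −11.2 |
| 0.01 | −15.8 |
| 0.0001 | −25.0 |

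For the first row: [log(60.5/40.5) − log(100.5/0.5)] − [log(10.5/90.5) − log(0.5/100.5)] = (0.40 − 5.30) − (−2.15 + 5.30) = −8.05. The answer depends on the constant, not the data.

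The article does not say that every case is still symptomatic at T0. If some are not, the case cell falls below 100%, but the control cell stays at 0% and the estimate is still not finite.

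A risk difference is finite. With T0 at 100% and 0%, however, cases can only fall and controls can only rise, so its sign is fixed. In the illustration it is (0.60 − 1.00) − (0.10 − 0) = −0.50.

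**Step 2: controls not asked at T1.** If absence is simply entered for controls, their change is 0 − 0 = 0 whatever happened to them. The comparison then contains only the change in cases.

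**Step 3: questionnaire scores.** Here the interaction is estimable. Suppose nothing truly changes and classification depends fully on the T0 score. The expected interaction is then −(1−ρ) × T0 gap, where ρ is the T0–T1 correlation. The article's retest ICCs give, per SD of gap:

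- pain catastrophizing, 0.88: at most 0.12 SD;
- anxiety, 0.84: at most 0.16 SD;
- physical activity, 0.74: at most 0.26 SD.

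These stand in for ρ only roughly. The anxiety figure is explicitly short-term, and no ICC is given for fatigue or functional status. An assumed three-year correlation of 0.50 would give 0.50 SD.

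A simulated population varied how far classification depends on the transient part of the T0 score. It assumed cases from the upper 20% and controls from the lower 50% of a noisy selection variable, and no true change. Rejection rates use a normal approximation with 100 per group, two-sided 0.05.

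| ρ | No dependence: bias, rejection | Half: bias, rejection | Full: bias, rejection |
|---|---|---|---|
| 0.90 | 0.00, 5% | −0.10, 37% | −0.20, 88% |
| 0.88 | 0.00, 5% | −0.12, 41% | −0.24, 93% |
| 0.84 | 0.00, 5% | −0.17, 55% | −0.31, 98% |
| 0.74 | 0.00, 5% | −0.28, 77% | −0.51, 100% |
| 0.50 | 0.00, 5% | −0.59, 99% | −0.98, 100% |

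Bias is in SD. The T0 gaps ran from about 1.3 to 2.0 SD and are assumptions.

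**The case against.** The strongest reply is that Objective 3 never names binary symptom presence as an outcome. It gives a general rule, and the sentence promising comparisons at each time point concerns severity measured by scales, for which the interaction exists. That is a fair reading of that sentence. It does not remove the problem: the third secondary objective lists symptoms alongside patient-reported outcomes, the Objective 3 heading names symptom evolution, and nothing excludes group-defining outcomes from the logit rule.

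Several stronger readings are tempting, and the article does not support them.

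- A reader might infer that symptoms in controls go wholly unmeasured. They do not: fatigue, function, sleep, mood and cognition are measured at both times without restriction to cases. Only the clause on presence and severity of persistent symptoms is worded for cases.
- A reader might infer that score interactions are driven by regression to the mean. Cutting the analysed score itself at T0 (top 20% against lower half, a gap of 2.20 SD) would give a spurious −0.22 SD at ρ = 0.9 and −0.88 SD at ρ = 0.6. But people are classified on reported symptom status lasting at least 12 weeks, not on a score cut-off. Many were classified before T0, through the patient association or as part of the retrospective cohort. The bias may therefore be zero.
- A reader might infer that cases can only improve and controls only worsen on scores. Nothing selects controls at the floor of any scale, and the scales leave cases room to worsen.
- A reader might count the lack of a prognostic model as an error. Prognosis is an expectation in the abstract, not a listed objective, and a condensed article may leave such a model to the full plan.

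Secondary Outcomes also points to Sociodemographic and Clinical Variables for the severity scales, which in fact appear in the sections after it. That is a drafting slip.

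**Conclusion.** The point holds for symptom presence and for any binary item that defines the groups. As written, the planned logit interaction has no finite estimate, and a risk-difference version has a fixed sign if all cases are symptomatic at T0. This follows from the control definition alone. The zero-change problem in controls is conditional: it arises if the Secondary Outcomes clause is followed literally at T1.

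For symptom-linked scores the conclusion is weaker. The contrast is valid to compute but may be biased towards convergence, by 0 up to about (1−ρ) times the T0 gap. The 0.12 to 0.26 SD per SD of gap is an upper figure that assumes full dependence of classification on the T0 score and takes retest ICCs from other scales. The article does not allow the actual size to be fixed, and the caveat is absent from Limitations.

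The scope is limited. This concerns a secondary objective of a study that describes its main aim as hypothesis-generating, and it does not touch the case-control analysis or the interaction for biomarkers and cognitive tests.

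**What to change.** 1. In Secondary Outcomes, state that the same symptom assessment is given to cases and controls at T1. T1 visits were scheduled for late 2025/early 2026, so this is urgent. Controls already seen without it should be recorded as missing, not as symptom-free.
2. In Objective 3, exclude group-defining symptom outcomes from the group × time contrast. Report instead, at T1, persistence or remission among cases and new symptoms among controls, each as a proportion with a 95% CI.
3. Keep group × time for the other outcomes. For symptom-linked scores such as fatigue and functional status, add a stated caveat on regression to the mean, in Objective 3 and in Limitations.
4. Correct the cross-reference for the severity scales.

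The cost is one short symptom form for controls, a few sentences of plan text, and giving up a differential-trajectory claim for symptom presence. A model among cases relating T0 factors to persistence at T1 would be a useful optional addition, not the correction of an error.
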